#### **4.1 Data analysis**

Data will be entered into an Excel sheet by the researcher. For checking data entry error, ten percent of data will be double entered. The error of 5% will be set, above which the data would be double entered. Descriptive statistics will be used to describe the characteristics of the hospitals, health professionals and patients. Between-group analysis will be used to establish if the two sets of groups are equivalent at baseline and at two months, four months, and six months. Depending on the type of data and whether they are normally distributed, the chi-square, Mann-Whitney U or independent t-test will be used. Within group differences, to establish whether each group has altered over time will be done and will include McNemar's test, sign test and the dependent t-test. As cluster sampling has been done, multi-level regression analysis will be done to control for the effect of clustering. For comparison of the diagnosis categories of both groups will be performed using Chi-square test to ensure that there is no association between diagnosis and groups. If necessary, sub-group analysis will be performed post-hoc to explore the impact of diagnosis on the outcome measures. The data will be presented in forms of tables, Scatterplots, and graphs.

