#### ***3.2.2.2 Sample size calculation***

It is anticipated that a 20% (8) sample of 40 district hospitals will allow the outcomes to be generalised to the other hospitals. In their study, Zegers et al. (2007) reviewing patients records in Dutch hospital, a random sample of 20% of the hospitals was selected and the results were

generalized. At each hospital all the relevant health professionals will be included in the training so the sample will be one of convenience. The primary outcome of this study will be the improved interprofessional practice within the district hospitals and comprehensiveness of the patients' records demonstrated by the scores. A sample size calculation will be done once the needed tools have been finalised and the mean and standard deviation calculated during a feasibility study. However as multi-level regression analysis will be done to account for the effect of clustering, a sample of 800 patients records (100 from each hospital) should allow for the analysis of at least 80 variables. This is a large number but, as it is anticipated that the effect size will be small due to the presence of so many confounding variables, a large sample size will be required to prevent a Type II error from occurring.

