### ***3.2.2.3 Recruitment and sampling method***

#### **District hospitals**

Cluster random sampling will be used by a blinded person to select the district hospitals within 40 districts of four provinces. It is anticipated that eight district hospitals will participate in this study. The sample will include Gahini hospital, Kiziguro hospital, Nemba hospital, Rutongo hospital, Remera Rukoma hospital, Nyanza hospital, Byumba hospital, and Ruhango hospital. The same individual will randomly allocate four hospitals on the experimental arm and other four hospitals on the comparator arm. The experimental hospitals will include: Gahini hospital, Nemba hospital, Rutongo hospital, and Remera Rukoma hospital. The comparator hospital will be composed of Kiziguro hospital, Ruhango hospital, Byumba hospital, and Nyanza hospital.

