#### **Medical records**

A stratified sampling method will also be used to select the patients' medical records that will meet the inclusion criteria to be involved in the study. It is anticipated to have a maximum of 100 patients' records per hospital. In each hospital, 100 patients' records will be audited at each occasion: baseline, two months, four months, and six months after intervention. Only the records of

discharged patients will be audited as well the records of discharged patients during two months of data collection.

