#### **4 Implementation strategy and procedure**

After selecting the hospital and allocation in either experimental or control, the meeting with the hospitals will be organised. One blinded research assistant who will be different from the one who has selected the hospitals will be trained to audit medical records of all discharged patients until a maximum of 100 records in each hospital have been audited. This person will be trained on basic ICF framework and needed information from the patients' folders, and how the records will be accessed and filled as well as the selection criteria. Research assistants will also collect data from health care professionals. The measurements will be taken at baseline (one month before training) and after training. Before training, the following measurement will be performed:

- Monitoring knowledge, attitudes and behaviour of the health care professionals towards interprofessional practice (Appendix v), holistic care (Appendix vii) and the impact of functioning and environmental context on patient well-being and quality of life (Appendix viii).
- Auditing the quality of patient's records, referral and discharge note (Appendix vi)

The researcher will again train another different research assistant who will help during training. One week after, the researcher and research assistant will plan the intervention. The training procedure will be based on that used during the feasibility study, but will be adapted as needed according to the experience from the feasibility study. After training the researcher and the trained health care professionals will hold a consensus meeting regarding implementation and how they can start introducing new forms to be used with the existing records. The control hospitals would receive no training during this time, but they will be given some basic introduction on ICF theoretical. For Experimental hospitals, two months follow-up will be done after training in order to check if there are some challenges and questions during practice. Again, the comparator hospitals will receive no follow up. Three time data collection also will be done at 2nd month, 4th month, and 6th month after training will be performed in both experimental and control.

After training, the following measurement will also be performed:

- Determining the satisfaction of health care professionals with ICF training and the method of implementation (Example: Appendix iv).

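### Section 4.1 compares the arms separately at each occasion and states no baseline-adjusted between-arm contrast and no lead occasion, although a baseline audit is taken in all eight hospitals

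*Combined protocol and SAP*

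**What the plan says.** Section 4.1 (Data analysis) holds the whole analysis plan for the trial phase.

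- **Between arms:** "Between-group analysis will be used to establish if the two sets of groups are equivalent at baseline and at two months, four months" (then at month 6). The tests are chi-square, Mann-Whitney U or independent t-test, depending on the data. No equivalence margin is given anywhere.
- **Case mix:** diagnosis categories are compared by a "Chi-square test to ensure that there is no association between diagnosis and groups". Post-hoc subgroup analysis by diagnosis may follow.
- **Over time:** change is tested within each arm only, by McNemar's test, sign test or dependent t-test.
- **Clustering:** multi-level regression is planned to control for it. Its covariates, time terms and arm contrast are not stated.

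Baseline data will exist. Under Medical records in section 3.2.2.3, up to 100 "records will be audited at each occasion: baseline, two months, four months, and six months after intervention". Section 4 adds: "The measurements will be taken at baseline (one month before training) and after training".

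Allocation is four against four: "The same individual will randomly allocate four hospitals on the experimental arm and other four hospitals on the comparator arm". No stratification or matching is described.

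Section 3.2.2.2 names the outcome without a time point: "The primary outcome of this study will be the improved interprofessional practice within the district hospitals and comprehensiveness of the patients' records".

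**The concern.** Three things are missing from the stated method.

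1. **A baseline-adjusted arm comparison.** With eight randomised units, the arms can differ noticeably at baseline by chance. Part of that difference persists to follow-up. Two within-arm tests of change do not compare the arms, so they do not deal with it.
2. **A valid reading of baseline.** A non-significant difference test does not show that groups are equivalent. With four hospitals per arm, a correctly clustered test would miss quite large imbalances. Under random allocation any baseline difference arises by chance, so the test answers no useful question. The diagnosis test has the same weakness.
3. **A lead occasion.** Three follow-up comparisons of equal standing give three chances of a false positive and leave the headline result open to choice after the data are seen.

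Section 3.2.2.2 expects a small effect, so both imbalance and lost precision could matter to the conclusion.

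**Working it through.** **The plan's own figures.** 0.20 × 40 = 8 hospitals, and 8 × 100 = 800 records. 800 / 80 = 10 records per variable, which appears to be the rule behind "a sample of 800 patients records (100 from each hospital) should allow for the analysis of at least 80 variables". The arithmetic reproduces. It is not a power calculation: no alpha, power, SD, effect size or ICC is given, and the calculation is deferred until after the feasibility study.

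**Inputs.** From the documents: 4 v 4 hospitals, 100 records per hospital per occasion, different discharged patients each time. Assumed: outcome SD = 1, two-sided alpha 0.05, ICC 0.01 to 0.10, cluster autocorrelation (CAC) 0.5 to 0.9, and a 0.5 SD effect for illustration. CAC is the correlation of the true hospital levels between two occasions.

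**Chance baseline difference.** Variance of a hospital mean: V = ICC + (1 − ICC)/100. SD of the difference between arms: √(2V/4).

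- ICC 0.01: V = 0.0199, SD = 0.10
- ICC 0.05: V = 0.0595, SD = 0.17
- ICC 0.10: V = 0.109, SD = 0.23

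**How much carries forward.** The correlation of baseline and follow-up hospital means is r = CAC × ICC / V. At ICC 0.05 and CAC 0.8, r = 0.04 / 0.0595 = 0.67. A one-SD imbalance of 0.172 then moves the unadjusted follow-up difference by an expected 0.67 × 0.172 ≈ 0.12 outcome SD.

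**Effect of adjustment.** The ratio of adjusted to unadjusted variance is (1 − r²) × [1 + 1/(6 − 2)] = 1.25 × (1 − r²). The factor 1.25 is the cost of estimating the slope from eight hospitals. Power is from simulated hospital means: unadjusted t-test on 6 df, baseline-adjusted analysis on 5 df.

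| ICC | CAC | r | Variance ratio | Power for 0.5 SD, unadjusted | Adjusted |
|---|---|---|---|---|---|
| 0.01 | 0.5 | 0.25 | 1.17 | 98% | 95% |
| 0.01 | 0.8 | 0.40 | 1.05 | 98% | 97% |
| 0.05 | 0.5 | 0.42 | 1.03 | 68% | 65% |
| 0.05 | 0.7 | 0.59 | 0.82 | 68% | 75% |
| 0.05 | 0.8 | 0.67 | 0.69 | 68% | 81% |
| 0.05 | 0.9 | 0.76 | 0.54 | 68% | 88% |
| 0.10 | 0.8 | 0.73 | 0.58 | 44% | 64% |

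Break-even for variance is r = √(1 − 1/1.25) = 0.45. For confidence-interval width, which also pays for the lost degree of freedom, it is about 0.52.

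**Three occasions.** If the tests were independent, familywise error would be 1 − 0.95³ = 14.3%. Follow-up means from the same hospitals are positively correlated, which lowers it. Simulation with correctly clustered tests gives about 10% (ICC 0.10, CAC 0.9) to 14% (low ICC).

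**The case against.** The strongest reply is that the multi-level model may already contain baseline. Section 3.2.2.2 speaks of at least 80 variables and many confounders, which implies covariates. That is fair. A reader might infer that the trial will never adjust for baseline, and the documents do not support this: they leave the covariates open. What remains is that no baseline term or lead contrast is stated. A list of up to 80 variables does not replace naming the one covariate most likely to matter with eight hospitals.

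Four other tempting readings go too far:

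- *Baseline serves only for a difference test.* It also enters the within-arm tests of change. These still do not compare arms.
- *Any non-significant follow-up result will be reported as equivalence.* The tests named are ordinary difference tests, and at 2, 4 and 6 months the wording may be loose. The criticism is firmest for baseline and for diagnosis, where the stated purpose is to rule out a difference.
- *Imbalance biases the trial or passes through in full.* The unadjusted estimate is unbiased over repeated allocations, and a correct cluster-level interval already reflects this variation. Only the fraction r of the realised imbalance carries forward.
- *Precision is certainly lost.* That depends on ICC and CAC, and the documents give neither. For a smaller effect the gain in power is also modest: for 0.2 SD at ICC 0.05 and CAC 0.8, about 17% to 22%.

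**Conclusion.** The concern holds as a gap in the stated method. The arms are compared one occasion at a time, no baseline-adjusted contrast is specified, no occasion leads, and difference tests are described as establishing equivalence. None of this depends on an assumed ICC.

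The size does depend on assumptions. At ICC 0.05 and CAC 0.7 to 0.9, adjustment cuts variance by about 18–19% to 46% net of slope estimation, and adds about 7 to 20 points of power for 0.5 SD. At ICC 0.01 or CAC 0.5 there is no material gain, or a loss of up to about 3 points for 0.5 SD. At ICC 0.01 power is already near its ceiling, so a smaller effect could lose somewhat more. Familywise error over the three occasions is about 10–14% even with clustering handled correctly.

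The change should be made, but the plan is open to repair and is not invalid.

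**What to change.** - Make the primary analysis one between-arm contrast in the multi-level model already planned: the Appendix v record score at one named occasion, for example six months. Adjust it for the hospital's baseline mean score, or model baseline as an outcome with a common mean for both arms.
- Use small-sample degrees of freedom suited to eight hospitals.
- Make the other two follow-up occasions secondary.
- Drop the word equivalent and the significance tests of baseline and diagnosis. Report baseline and case mix descriptively by arm.
- Adjust at hospital level. Each audit uses different discharged patients, so there is no patient-level baseline to pair with.
- Do not require adjustment for ward or diagnosis unless they are recorded as categories. The Appendix v form has no ward field, and its diagnosis item is a Yes/No/N/A entry within the checklist being scored.
- Settle the choice with the deferred sample size calculation, over a range of ICC and CAC.

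The cost is mainly analysis-plan wording, because the baseline audit is already planned. The Appendix v score also needs a stated scoring rule, which the documents do not give. Statistically the price is one degree of freedom, and a small loss of power if ICC or CAC proves low.

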## **3.2 Methodology - Intervention study**

### **3.2.1 Study design**

A Cluster Randomised Control Trial (CRCT) using a pragmatic study design will be used in this study. Cluster randomised controlled trials (CRCTs), is a design used in health research services whereby clusters are randomised to intervention groups. This design is primarily used to avoid contamination between the control and experimental groups when a single setting (such as a ward) is utilised (Hemming, Girling, Sitch, Marsh, & Lilford, 2011). This design will be appropriate to compare the outcome of the intervention between the experimental and comparator group.

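### Section 4.1 compares arms of randomised hospitals with tests that ignore clustering, and does not say whether these or the multilevel model decide the trial

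*Combined protocol and SAP*

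**What the plan says.** Section 3.2.1 sets the design: "A Cluster Randomised Control Trial (CRCT) using a pragmatic study design will be used in this study". Section 3.2.2.2 takes "a 20% (8) sample of 40 district hospitals", and section 3.2.2.3 (District hospitals) adds: "The same individual will randomly allocate four hospitals on the experimental arm and other four hospitals on the comparator arm". Under Medical records in the same section, "In each hospital, 100 patients' records will be audited at each occasion", and 100 is described there as a maximum.

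Section 4.1 plans between-group comparisons at baseline and at two, four and six months, and names the tests: "Depending on the type of data and whether they are normally distributed, the chi-square, Mann-Whitney U or independent t-test will be used". It attaches no cluster adjustment to them. It then says: "As cluster sampling has been done, multi-level regression analysis will be done to control for the effect of clustering". Section 3.2.2.2 also mentions the multilevel regression, when it justifies the number of records. Neither section gives the model an outcome, time point, random-effects structure, estimator or degrees of freedom, or ranks it against the simple tests.

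Section 4.1 also compares diagnosis categories between arms "using Chi-square test to ensure that there is no association between diagnosis and groups".

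**The concern.** Only eight units are randomised. Records from one hospital share staff, forms and recording habits, and the intervention acts on the whole hospital. A two-sample test on individual records treats 400 per arm as independent, so it understates the standard error of the arm difference. Someone following section 4.1 literally would produce unadjusted and multilevel p-values for the same comparison, with no rule for choosing between them. If the unadjusted ones were used, an ineffective programme could too easily be reported as effective.

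Two related points follow. With eight hospitals, a multilevel model also needs a small-sample reference distribution, and none is specified. The diagnosis chi-square ignores clustering as well, and a non-significant result cannot show balance.

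**Working it through.** **The plan's own figures.** 0.20 × 40 = 8 hospitals and 8 × 100 = 800 records. The plan says that "a sample of 800 patients records (100 from each hospital) should allow for the analysis of at least 80 variables"; 800 / 10 = 80, where 10 records per variable is inferred. These reproduce, but they are not a power or error-rate calculation.

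**Inputs.** Four hospitals per arm (3.2.2.3); m = 100 records per hospital per occasion (3.2.2.3, a maximum). Assumed: two-sided 5%, since no significance level is stated, and a between-hospital ICC of 0.001 to 0.20, since the only ICC planned is for rater agreement (3.1.5). Equal cluster sizes and a single time point throughout.

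**Unadjusted test on records.** Design effect DE = 1 + (m − 1) × ICC; true size = 2 × [1 − Φ(1.96 / √DE)].

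| ICC | DE | True size |
|---|---|---|
| 0.001 | 1.10 | 6.2% |
| 0.005 | 1.50 | 10.9% |
| 0.01 | 1.99 | 16.5% |
| 0.02 | 2.98 | 25.6% |
| 0.05 | 5.95 | 42.2% |
| 0.10 | 10.9 | 55.3% |
| 0.20 | 20.8 | 66.7% |

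Size passes 10% once the ICC exceeds about 0.004. Simulation at ICC 0.01, 0.02, 0.05 and 0.10 gave 17%, 26%, 42% and 56% for the t-test; 19%, 26%, 42% and 54% for Mann-Whitney; and 13%, 20%, 34% and 47% for chi-square on a dichotomised score.

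**Staff questionnaires.** Clusters are smaller. At ICC 0.05, m = 20 gives DE = 1.95 and size 16%; m = 50 gives DE = 3.45 and size 29%.

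**Multilevel model at one time point.** The arm difference has 8 − 2 = 6 degrees of freedom between hospitals, so the critical value is 2.45 rather than 1.96.

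- REML with a normal reference: P(|t₆| > 1.96) = 9.8%; simulated 8.4% to 9.8% for ICC 0.01 to 0.20.
- ML with a normal reference: P(|t₆| > 1.96 × √(6/8)) = P(|t₆| > 1.697) = 14.1%; simulated 11.1% to 14.2%.
- At ICC 0 to 0.001, both are at or below about 5%.
- t on 6 df: simulated 4.6% to 5.4% at every ICC from 0 to 0.20.

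**Joint model of the occasions.** Suppose ICC 0.05 and a between-occasion hospital correlation of 0.8, so that 0.04 of the variance is persistent and 0.01 is hospital-by-time. With only a hospital intercept, the 0.01 goes into the residual (0.95 + 0.01 = 0.96). The true variance of a hospital mean, net of the intercept, is 0.01 + 0.95/100 = 0.0195; the model takes it as 0.96/100 = 0.0096. The ratio is 2.03, and 2 × [1 − Φ(1.96 / √2.03)] is about 17% for an arm-by-time test.

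**Diagnosis chi-square.** Assume three categories (the documents give no number), 800 records and the same DE. Size is P(χ²₂ > 5.99 / DE) = exp(−2.996 / DE): 22%, 37% and 60% at ICC 0.01, 0.02 and 0.05, after a fair randomisation.

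**The case against.** The strongest reply is that the authors recognise clustering. They plan a multilevel regression in section 4.1 and mention it in section 3.2.2.2, in the paragraph that names the primary outcome. On that reading it is the intended analysis of the records and the simple tests are secondary. A reader might infer that the trial will be decided on unadjusted tests, so that its main p-value is wrong. The documents do not say that. They set no order between the analyses, and section 4.1 names no unit of analysis; record-level testing is the likely reading, not a stated one.

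A reader might also infer that eight clusters by themselves push the multilevel model far above 5%. That is not supported either. The 8-14% arises only with a normal reference, and the plan does not say which reference will be used. This part is a missing specification.

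The sizes also rest on an assumed ICC and significance level and on the maximum of 100 records. Near an ICC of 0.001 the inflation is slight, and for staff it is smaller.

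What remains is that the unadjusted tests are the only ones tied to the between-arm comparison at named times, and nothing makes them subordinate to the model.

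**Conclusion.** The point holds as a fault in section 4.1: it assigns between-arm comparisons in a hospital-randomised trial to tests without cluster adjustment, and leaves their standing against the multilevel model undefined. If those tests are run on 100 records per hospital at a two-sided 5% level, the false-positive rate at one time point is about 6% to 55% for ICC 0.001 to 0.10, and at least 11% once the ICC reaches 0.005. Testing at three follow-up times would add to this and is not counted. The multilevel model is adequate for a single time point if given a small-sample correction, which the plan has yet to specify. The diagnosis chi-square should not serve as evidence of balance. The correction should be made before any arm comparison is run.

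**What to change.** In section 4.1:

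1. Remove the chi-square, Mann-Whitney and independent t-tests as between-arm inference; keep descriptive summaries by arm.
2. Make a cluster-level analysis the sole arm comparison for both records and staff, and name the primary time point. Use either a multilevel model with a hospital random effect, REML and Kenward-Roger or Satterthwaite degrees of freedom (about 6), or a permutation test over the C(8,4) = 70 possible allocations. The smallest two-sided p for the latter is 2/70 = 0.029.
3. If occasions are modelled jointly, add a hospital-by-time random effect, and a person-level effect for repeated staff measures.
4. Report diagnosis by arm descriptively and drop its chi-square. Adjust for diagnosis category or ward only if these are recorded for each audited record. The audit form (Appendix v) has no ward field and records diagnosis only as a Yes/No/N/A tick; ward appears on the staff questionnaires.

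The cost is a rewording, possibly two form fields, and a check that the software offers the correction (STATISTICA is named only for the feasibility study). The statistical cost is wider intervals. With SE = √[(2/4) × (ICC + (1 − ICC)/100)] and a t-test on 6 df, the difference detectable with 80% power is 0.34, 0.41, 0.58 and 0.79 SD at ICC 0.01, 0.02, 0.05 and 0.10. Treating 400 records per arm as independent would suggest √(2/400) × (1.96 + 0.84) = 0.20 SD. The sample size calculation that section 3.2.2.2 defers should use the clustered figures.

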### 3 Methodology - Feasibility study

Prior to the main study, a feasibility study will be carried out in one selected district hospital. This is Nyamata hospital which has been selected purposively. Nyamata Hospital has the capacity of 164 beds, 14 medical doctors, 3 social workers, 79 nurses, 3 physiotherapists, and 2 nutritionists(Nyamata Hosiptal, 2012). A feasibility study is usually used to determine if the intended intervention is appropriate for further study (Taylor, Russ-Eft & Chan, 2005). This study will enable the researcher to answer the question “Can this study be done?” This study will also enable the researcher to estimate some important parameters that will be needed in the design of the main study. These could include the time needed to collect and analyse data, willingness to participate, availability and suitability of data, feasibility and duration of training, and designing a suitable outcome measure. The feasibility study will also determine if patients’ records reflect the actual practice in the hospitals.

[figure not shown]

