### **3.2.2 Population**

The population for the study will be the same as feasibility study. This will include the above mentioned health care professionals and patients' records of discharged patients. According to the reports from different hospitals, the average number of beds in each hospital is 182, Doctors (General practitioners) is 10, 80 Nurses, two Physiotherapists, one Mental Health/Clinical Psychologist, and one social worker. In general, these are the health professionals that may be found in District hospitals of Rwanda who have responsibility, at some extent, to provide services on the patients in above mentioned wards.

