#### **Health care professionals**

Convenience sampling will be used to recruit the health care professionals who will participate in this study. All medical doctors and nurses who will be working in the selected district hospital (surgical, medical and paediatric wards) during the period of the study will be recruited. The sample will be also composed of all physiotherapists, social workers, mental health/psychologists, and nutritionists/dietetics who will be working in the selected district hospitals during the period of intervention and data collection.

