| Health professional 

1. Medical doctor 
2. Physiotherapist 
3. Nurses 
4. Social Worker 
5. Mental Health Nurse 
6. Clinical psychologist 
7. Nutritionist/Dietetic  | Ward 

1. Medical 
2. Surgical 
3. Pediatric  | Level of education 

1. A2 
2. A1 
3. A0 
4. Masters 
5. Other: 
Specify:..... | Gender 

1. Male  2. Female 

Age: .....Years

Years of Experience:
.....Years |
|-----------------------------------------------------------------------------------------------------------------------------------------------------------------------------------------------------------------------------------------------------------------------------------------------------------------------------------------------------------------------------------------------------------------|-----------------------------------------------------------------------------------------------------------------------------------------------------------------------------|-----------------------------------------------------------------------------------------------------------------------------------------------------------------------------------------------------------------------------------------------------------------------|-------------------------------------------------------------------------------------------------------------------------------------------------------------------------------------------------------------|

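### The plan does not say that profession will be used in analysing the staff knowledge and attitude scores, although every staff form records it and nurses will probably dominate a pooled score

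*Combined protocol and SAP*

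**What the plan says.** **Tests.** Section 4.1 covers all outcomes together. For differences between arms at baseline and at two, four and six months it says "Depending on the type of data and whether they are normally distributed, the chi-square, Mann-Whitney U or independent t-test will be used". Change within an arm is tested with paired methods. A multi-level regression is added to deal with clustering; neither its covariates nor the outcomes it applies to are listed. Characteristics of the health professionals are to be described. The only subgroup factor named is diagnosis, which belongs to patient records.

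**Forms.** The attitude, knowledge and satisfaction forms (Appendices ii, iii and iv) each open with a field headed "Health professional", with seven options starting at "1. Medical doctor".

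**Staffing.** Section 3.2.2 gives averages for a whole hospital: "Doctors (General practitioners) is 10, 80 Nurses, two Physiotherapists, one Mental Health/Clinical Psychologist, and one social worker". Section 3 gives the feasibility hospital: "14 medical doctors, 3 social workers, 79 nurses, 3 physiotherapists, and 2 nutritionists".

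**Who is enrolled.** Section 3.2.2.3 takes doctors and nurses from the surgical, medical and paediatric wards only, but places no such limit on the other groups: "The sample will be also composed of all physiotherapists, social workers, mental health/psychologists, and nutritionists/dietetics". Sampling is by convenience, and section 4.2.1 makes participation voluntary. Section 4 puts contact with the hospitals after allocation, and section 4.2.1 gives staff a different information letter in each arm.

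**Primary outcome.** Section 3.2.2.2 names interprofessional practice and the completeness of patient records, not the staff scores.

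**The concern.** One objective in section 1.4.2 is to improve staff knowledge and attitudes about interprofessional practice. Sections 1.1.1 and 1.2 motivate the trial by the separateness of the professions, and section 1.2 says that use of the ICF is limited especially outside rehabilitation. The plan therefore has its own reasons to expect scores to differ by profession. Five of the 21 attitude items (4, 6, 13, 16 and 18) concern the authority or role of physicians, on which doctors and nurses may well differ.

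Two things are at stake if profession is left out.

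- **Meaning.** An unstratified staff score mostly reflects the largest group. A change confined to doctors and allied staff could be almost invisible, and a change confined to nurses could be read as a change across the team.
- **Comparison of arms.** Staff decide whether to take part after their hospital's arm is fixed, and there are only four hospitals per arm. The share of doctors and allied staff who respond can differ between arms by chance or by uptake. The stated two-sample tests would carry that difference into the result.

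Leaving the covariates open also lets them be chosen after the data are seen.

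**Working it through.** The documents give no staff sample size, nurse share, SD, effect size, alpha or power for the staff scores, so there is no stated figure to reproduce. The 800 in section 3.2.2.2 is 8 x 100 patient records and does not concern staff.

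**1. Nurse share of listed staff.**
- Section 3.2.2: 10 + 80 + 2 + 1 + 1 = 94; 80/94 = 85.1%. Nutritionists are recruited but are not in this average. Adding one or two gives 80/95 = 84.2% or 80/96 = 83.3%.
- Feasibility hospital: 14 + 3 + 79 + 3 + 2 = 101; 79/101 = 78.2%.

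**2. Nurse share of enrolled staff (assumed ward fractions).** Let a fraction f_n of nurses and f_d of doctors work on the three ward types, and let all 4 to 6 allied staff join. Share = 80 f_n / (80 f_n + 10 f_d + allied).

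| f_n | f_d | Share, 4 allied | Share, 6 allied |
|---|---|---|---|
| 1 | 1 | 80/94 = 85% | 80/96 = 83% |
| 0.5 | 0.5 | 40/49 = 82% | 40/51 = 78% |
| 0.25 | 0.25 | 20/26.5 = 75% | 20/28.5 = 70% |
| 0.5 | 1 | 40/54 = 74% | 40/56 = 71% |
| 0.25 | 1 | 20/34 = 59% | 20/36 = 56% |

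Nurses are the majority in every case, but 85% is the top of the range.

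**3. What a pooled score would show.** Pooled effect = sum of (share x effect in that group).
- Weights 0.851 and 0.149: 0.5 SD in nurses only gives 0.851 x 0.5 = 0.43 SD; 0.5 SD in all others and none in nurses gives 0.149 x 0.5 = 0.07 SD.
- Weights 0.70 and 0.30: the same two cases give 0.35 SD and 0.15 SD.
- A 1 SD gain in every doctor moves the pooled mean by 10/94 = 0.11 SD.

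**4. Effect of mix on the arm difference (all inputs assumed).** Let the non-nurse share vary between hospitals with SD s = 0.05 to 0.10, the gap between professions be g = 0.5 to 1 SD, respondents per hospital m = 60, and ICC = 0.01 to 0.05. The part of the variance due to mix is s²g² / [s²g² + ICC + (1 − ICC)/m].
- Lowest: 0.000625 / (0.000625 + 0.05 + 0.95/60) = 0.9%.
- Highest: 0.01 / (0.01 + 0.01 + 0.99/60) = 27%. This falls to about 25% when shares are kept from going below zero.
- Simulation of 4 v 4 hospital means over the same grid gave 0.7% to 24.4%.
- If the mean non-nurse share differed between arms by 10 points, the arm difference would shift by 0.10 x g = 0.05 to 0.10 SD.

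**5. What separate results could support.** Smallest detectable difference = (1.96 + 0.84) x sqrt(2/n), with n per arm from section 3.2.2 (all enrolled, four hospitals), assumed two-sided alpha 0.05 and power 80%, and no clustering.

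| Group | n per arm | Detectable difference |
|---|---|---|
| Nurses | 320 | 0.22 SD |
| All non-nurses | 56 | 0.53 SD |
| Doctors | 40 | 0.63 SD |
| Others | 16 | 0.99 SD |

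Clustering and the ward restriction make each of these larger.

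**The case against.** The strongest reply is that silence is not a rule. The plan nowhere says that staff scores will be compared as one mean, and two of the three tests it names do not compare means. The multi-level model has no covariate list, so profession could be in it; section 3.2.2.2 expects many confounders and a regression with many variables, although it is speaking of patient records. Professional mix would be described, and the baseline comparison could include it. All of this stands: the documents support only that use of profession is not stated, not that it is ruled out.

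A reader might go further and infer that 85% of participants are nurses and that any staff result is in effect a nurse result. The documents do not support that. The 85% is whole-hospital staffing, while enrolment restricts doctors and nurses by ward and takes all allied staff. A pooled average over the staff who were offered training is also a legitimate quantity, and pooling does not in itself bias a randomised comparison. Nor does the point reach the primary outcome, which includes the record audit.

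The precision gain is fair ground for doubt too: every input is assumed, and the range runs from negligible to material.

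What the reply does not remove is that the only stated purpose of the model is clustering, that the stated tests are unadjusted, and that volunteers join after allocation in eight hospitals. Description and a baseline test do not adjust the comparison.

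**Conclusion.** The point holds as a minor, nearly free improvement to the analysis of staff knowledge and attitude scores. Profession is collected on every staff form, and no stated analysis of those scores adjusts for it or stratifies by it. Nurses are 85% of listed hospital staff; among enrolled staff the share is roughly 70% to 85% if doctors and nurses are restricted equally by ward, and could be as low as 56% to 59% if all doctors but only a quarter of nurses qualify. They would probably dominate a pooled score, so that a 0.5 SD change limited to the other professions would appear as about 0.07 to 0.15 SD over the 70% to 85% range.

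The risk to the arm comparison is noise, and possibly bias, from differing professional mix among post-allocation volunteers. Its size is not known from the documents: mix would account for about 1% to 24% of the variance of the arm difference under the assumed inputs. This does not show that the trial's staff results will be wrong or that they will describe nurses alone.

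**What to change.** State in section 4.1 that, for the knowledge and attitude scores, the analysis is the planned multi-level model with profession group (nurse, doctor, other) as an individual-level fixed effect, or equivalently that scores are adjusted for profession before hospital means are compared. Make this the staff-outcome analysis in place of the unadjusted tests. Because the covariate is at the individual level, it uses none of the few hospital-level degrees of freedom.

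Adjustment deals with differences in mix between arms; it does not change the fact that the average effect is weighted towards nurses. So also report the arm difference with its confidence interval for nurses and for non-nurses, splitting doctors from others where numbers allow. Label these as descriptive, and make no claim of change or no change in a profession from its separate result: with about 40 doctors and 16 others per arm at most on the listed averages, a null result there means little. Show the number of respondents by profession, hospital and arm.

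The cost is a sentence or two in the analysis section and one more table, with wide intervals for the small groups. No new data are needed. Adjustment cannot correct for selective volunteering within a profession.
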